### Interim analyses {21b}

There will be no planned formal interim analyses of the primary and secondary outcomes. However, we will conduct further analyses of secondary outcomes at the completion of the 52-week follow-up for all the patients.

### Methods for additional analyses (e.g. subgroup analyses) {20b}

We will use data collected during this study for further analyses investigating the following topics:i.Image analysis—a CoreLab will perform imaging analysis of technical outcomes and anatomy as seen on the 2 postoperative CTs.ii.Health economic analysis will be performed to examine the cost-effectiveness of the Cydar EV system. This will include an analysis of the systems efficiency that the Cydar EV system may allow.iii.Quality of life between the two groups will be assessed using the area under the curve method.

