#### Secondary outcomes

Procedural efficiency:Anaesthetic duration—the time between the beginning of induction and the end of emergence. This will be documented at the time of the procedure by the local research team in minutes.X-ray dose per procedure—fluoroscopy time (FT) (seconds), dose area product (DAP) (Gy.cm2) and cumulative air kerma (CAK) (mGy) should be recorded and documented at the time of the procedure by the local research team. The imaging system used should also be recorded.Contrast dose per procedure—the volume (ml) and concentration (mgI/ml) of the iodinated contrast material used should be recorded by the local research team at the time of the procedure in minutes.Consumable use in the operating theatre for endovascular aortic aneurysm repair—name of device, unit and quantity used, blood products used; details to be completed by nurse in the operating theatre or research nurse at the time of the procedure.Technical success:Proximal and distal seal zone at least 10mm and no evidence of endoleak. This will be documented by the imaging CoreLab team on review of the CT images acquired post-operatively and at 4–12 weeks and at 52 weeks.Patient outcomes:Length of ICU/HDU admission—date and time from admission to date and time of discharge from ICU/HDU; documented by the local research team during the time of admission; ICU and HDU admissions should be documented separatelyPostoperative length of hospital stay—date of procedure to date of discharge from hospital (nights); documented by the local research team during the time of admission.30-day mortality—death of the participant within 30 days of the primary procedure; documented by the local research team; to include date of death (dd/mm/yy) and cause.Re-intervention—any procedure open surgical or endovascular undertaken within 1 year of the primary endovascular aortic aneurysm repair procedure (binary outcome). The type, timing, and number of procedures should also be recorded by the local research team.Adverse events—hospitalisation for any reason within one year of the primary endovascular aortic aneurysm repair; the type of event should be documented and classified as one of the following: musculoskeletal, urological, neurological, ophthalmological, cardiovascular, gastro-intestinal, hepato-pancreato-biliary, dermatological, or other by the local research team, with information captured to understand if linked to re-intervention. For each hospitalisation, the following should also be captured:i.Day case, elective, non-electiveii.Length of hospital stay—date of admission to date of discharge (nights)iii.Length of ICU/HDU admission (if applicable)—date and time from admission to date and time of discharge from ICU/HDUQuality of life—differences in quality of life between intervention and the comparator group and changes in quality of life post-surgery will be measured using data from the patient-completed EQ5D-3L [11] instrument. EQ-5D-3L is a validated measure of health-related quality of life, consisting of a five-dimension health status classification system and a separate visual analogue scale. EQ-5D-3L data will be obtained through face-to-face or telephone interview with the participant at baseline, pre-discharge, 4–12 weeks, and at 12 months follow-up.Cost-effectiveness, as assessed by:Total resource use and costsQuality-adjusted life years (QALYs)—quality of life will be measured by the EQ-5D-3L instrument as described above. In order to be used in the calculation of quality-adjusted life years (QALYs), the EQ-5D-3L dimension scores will be converted to utilities using the relevant value set for England. Quality-adjusted life years (QALYs) gained in both groups, over the time horizon of the trial, will be calculated using the area under the curve method.Incremental cost per QALY

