## Assignment of interventions: allocation

### Sequence generation {16a}

Once baseline assessments are complete, participants will be randomised in a 1:1 ratio using the method of minimisation. Randomisation is at the patient level and is performed using a web-based bespoke randomisation system set up by the King’s Clinical Trials Unit (KCTU) at King’s College London. Randomisation is minimised by the following factors:SurgeonProcedure urgency: emergency or electiveProcedure type: simple (repair of infra-renal aneurysm ± internal iliac embolisation) or complex (all other types of AAA and TAAA repair, to include branched and fenestrated devices)

The procedure is as follows: on receipt of the baseline questionnaire, the trial coordinator electronically submits details of each participant to the CTU. This includes participant ID number, site, initials, and date of birth. The system immediately notifies the relevant study nurse and records the randomisation outcome. The trial coordinator does not receive the randomisation outcome.

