#### Statistical methods for primary outcome

As the primary outcome is procedure duration and we envisage 7.5% loss of patients between randomisation and procedure, the primary analysis will be a per-protocol (PP) analysis based on procedure time. The primary analysis will be conducted after completion of first follow-up (at 4–12 weeks) which will include procedure time as well as the secondary outcome data available at this time. Sensitivity analysis with multiple imputation for missing data will also be conducted alongside the per-protocol analysis. No significance tests will be performed for baseline comparison. The primary outcome measure is likely to have a skewed distribution and therefore if necessary and possible the data will be normalised using an appropriate transformation. The data will then be analysed using linear regression techniques with stratification (minimisation) factors included as covariates. If a suitable transformation cannot be found, the data will be analysed using quantile regression to allow us to include the addition of the stratification factors as covariates.

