#### Statistical methods for secondary outcomes

A similar analysis will be undertaken for the secondary outcomes including quality of life scores. Binary outcomes will be compared between arms using logistic regression adjusting for stratification factors. Outcomes will be reported as adjusted differences in means (or median) or odds ratios for continuous and binary data respectively. All tests will be two sided and will be assessed at the 5% significance level. Safety outcomes will be reported as patient proportions and rates within and between arms with 95% confidence intervals using exact methods where appropriate.

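### The model carried over to quality-of-life scores names only the minimisation factors; baseline EQ-5D, though collected, is named as a covariate nowhere

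*Protocol article*

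**What the plan says.** All references are to the protocol article.

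- **Collection.** Under Secondary outcomes, EQ-5D-3L is obtained "at baseline, pre-discharge, 4–12 weeks, and at 12 months follow-up". The same entry says that between-group differences and "changes in quality of life post-surgery will be measured using data from the patient-completed EQ5D-3L", without saying how the baseline value enters.
- **Model.** Statistical methods for primary outcome specifies, after any transformation, "linear regression techniques with stratification (minimisation) factors included as covariates", with quantile regression as the fallback. Statistical methods for secondary outcomes then states: "A similar analysis will be undertaken for the secondary outcomes including quality of life scores".
- **Minimisation factors.** Sequence generation {16a} lists, under "Randomisation is minimised by the following factors", the surgeon, emergency versus elective, and simple versus complex procedure. None is a quality-of-life measure.
- **AUC and QALYs.** Under Secondary outcomes, QALYs "will be calculated using the area under the curve method". Methods for additional analyses {20b} adds: "Quality of life between the two groups will be assessed using the area under the curve method". Neither place names a model or a covariate.

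**The concern.** The template model was written for procedure duration, which has no pre-randomisation value, so it has no baseline term. Carried over as written, it gives EQ-5D scores a model without their own baseline measurement, which is usually among the strongest predictors of a later score. Two things follow. Variance that baseline could explain stays in the residual. A chance difference between arms in baseline utility also stays in the estimated effect, because later scores correlate with baseline.

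The second point matters most for the economic result. The QALY difference is the denominator of the incremental cost per QALY, and cost-effectiveness is part of the trial's stated overarching aim.

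**Working it through.** **The plan's own figure.** The article states a sample size for procedure time only, and none for EQ-5D or QALYs. With the control CV 69.2/132.1 = 0.524, log-scale SD √ln(1 + 0.524²) = 0.492 and difference ln 1.2 = 0.182, two-sided 5% and 90% power need 154 per arm (normal approximation) or 155 (t). Rounding the CV to 0.52 gives 152 or 153. The stated 153 is reproduced within rounding, and 153/(1 − 0.10) = 170. I take 153 per arm as the number with EQ-5D; this is an assumption, and fewer may remain at 12 months.

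**Assumed inputs.** The documents give no EQ-5D SD or correlation. I assume a utility SD of 0.25 (range 0.20 to 0.30), equal correlation r = 0.3, 0.5 or 0.7 between all time points, discharge at day 5 and the middle visit at week 8.

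**Single follow-up score.** Adjusting for baseline multiplies the residual variance by 1 − r² and the SE by √(1 − r²).

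| r | Variance factor | Variance saved | SE saved | Equivalent extra patients, 1/(1 − r²) − 1 |
|---|---|---|---|---|
| 0.3 | 0.91 | 9% | 4.6% | 10% |
| 0.5 | 0.75 | 25% | 13.4% | 33% |
| 0.7 | 0.51 | 49% | 28.6% | 96% |

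These are upper figures at each r, because they ignore what urgency and procedure type, already in the model, explain of baseline EQ-5D.

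If baseline were instead meant to enter through simple change scores, the variance factor would be 2(1 − r) = 1.40, 1.00 and 0.60. That is worse than 1 − r² at each of these correlations.

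**Size of chance imbalance.** The SE of the baseline difference is SD × √(2/153) = 0.25 × 0.1143 = 0.0286. For SD 0.20 to 0.30 it is 0.023 to 0.034, so the 95% chance limit (1.96 SE) is 0.045 to 0.067.

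**Carry-over into QALYs.** The trapezoid weights, in years, are 0.0068 (baseline), 0.0767 (pre-discharge), 0.4932 (week 8) and 0.4233 (12 months). The slope of the QALY on baseline utility is w₀ + r(1 − w₀) = 0.305, 0.503 and 0.702, close to r itself.

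- One-SE imbalance: 0.0286 × r gives about 0.009 (r = 0.3) to 0.020 QALY (r = 0.7).
- Imbalance of 0.05: a shift of about 0.015, 0.025 or 0.035 QALY.
- Direct part of that shift: 0.0068 × 0.05 = 0.0003 QALY. If the pre-discharge score is left out, baseline's weight becomes 0.0767 and the direct part 0.004. The shift therefore comes mainly through correlation, not through baseline's own place in the area.

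**QALY precision at SD 0.25.** The SE falls from 0.0221 to 0.0204 (8%), 0.0242 to 0.0194 (20%) and 0.0260 to 0.0166 (36%) for r = 0.3, 0.5 and 0.7.

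**The case against.** The strongest reply is that nothing here is stated wrongly. The article says *similar*, not identical, and does not exclude a baseline covariate. It is a condensed account, it refers to a statistical analysis plan that is not shown, and covariates for a secondary outcome are often settled there. The QALY regression may sit in that plan or in a health economics plan. The reference to post-surgery change suggests that baseline is meant to be used somehow.

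Much of this stands. A reader might infer that the QALY comparison adjusts for the minimisation factors alone, but the article states no adjustment set for AUC or QALYs; that reading stretches the secondary-outcome sentence onto a cost-effectiveness result. A reader might also infer bias, but under randomisation the unadjusted difference is unbiased and its standard error already allows for chance imbalance. Nor do the documents show that imbalance could reverse the QALY result, since they give no expected QALY difference. It would also be too strong to say that nothing balances baseline EQ-5D. Urgency and procedure type are minimised, and because symptomatic and ruptured cases are eligible, urgency plausibly tracks baseline health.

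What does not stand is that the matter is wholly left open. For quality-of-life scores the article does choose a model and does name its covariates, and baseline EQ-5D is not among them.

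**Conclusion.** The point holds in a limited form. As written, the model for quality-of-life scores names surgeon, urgency and procedure type and omits a baseline value that the trial already collects; for AUC and QALYs the covariates are unstated. The consequence is lost precision and exposure to chance imbalance, not bias.

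The gain from adjustment could be small at r = 0.3 and substantial at r = 0.7. The size rests on the assumed SD, correlations, visit timing and number with data, and the precision gain shrinks if covariates already in the model explain part of baseline EQ-5D. The point concerns secondary and economic outcomes only; the procedure-time analysis and the sample size do not change.

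**What to change.** In Statistical methods for secondary outcomes, state that quality-of-life models include the baseline value of the score being analysed (EQ-5D utility, or VAS for the VAS analysis) together with the minimisation factors. State that the AUC/QALY comparison feeding the incremental cost per QALY is adjusted for baseline utility in the same way. If the analysis plan or health economics plan already says this, a cross-reference is enough. This also settles how baseline enters the promised assessment of change.

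The cost is wording only, because the data are already collected. It should be fixed before outcome data are inspected, which is the article's own deadline for the analysis plan.

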### Methods in analysis to handle protocol non-adherence and any statistical methods to handle missing data {20c}

Compliance with intervention will be recorded in the source data worksheets and transcribed to the EDC system. Reasons for non-compliance would include device failure, surgeon error, or failure to communicate correct randomisation allocation to the surgeon. The patient could only impact compliance if they express a wish to withdraw between randomisation and surgical procedure. Missingness will be reported and reasons for missingness explored. Although a low percentage of missing data is anticipated, a sensitivity analysis of the primary outcome will be undertaken in order to assess the impact of the exclusion of participants with missing intraoperative data in the primary analysis. In this view of the sample size, a modelling approach will be taken rather than multiple imputation.

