Patient benefit was observed by a significant reduction in the amount of X-rays used, with a mean reduction in X-ray fluoroscopy screening time of 35% (*p* = 0.013), a 41% reduction in the amount of iodinated contrast used (*p* = 0.008), and a nearly 1 h reduction in mean operating time (17%, *p* = 0.06) [9]. A further prospective observational cohort study of 119 patients was conducted at Duke University Medical Centre. This reported a mean reduction in procedure time of 17% (*p* = 0.04), with Cydar-EV and a reduction in the number and duration of unexpectedly very long operations [10]. There was also significantly better renal function after the procedure and at 30 days, an indirect metric of the effect of less nephrotoxic contrast agent, and better device positioning. There are no known additional risks of using Cydar EV in comparison to standard treatment. Interruption of the Internet connection during the procedure is possible but rare (< 0.001%).

Demonstrating Cydar-EV improves the outcomes of endovascular surgery at a lower cost for the NHS would be a key demonstration of the potential of digital technology (cloud-computing, big-data, AI) to improve precision and consistency of outcomes for image-guided surgery. It would establish a new concept of data-guided surgery to deliver intelligent planning and outcome analysis, aggregating and learning from existing data to improve the precision, consistency, and transparency of patient outcomes for stakeholders across the NHS: patients, commissioners, hospitals, and clinical teams.

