### Strategies to improve adherence to interventions {11c}

Reasons for non-compliance could include Cydar EV device failure, Internet failure, surgeon error, failure to communicate correct randomisation allocation to the surgeon, cross-over, and failure to upload images to Cydar EV, or a non-Cydar-trained surgeon performs the procedure. The patient could impact compliance if they express a wish to withdraw between randomisation and surgical procedure or in the event of death.

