### Adverse event reporting and harms {22}

Adverse events will be categorised as per the medicines for human use (Clinical Trials) regulations 2004 and amended regulations 2006. Where any adverse event occurs, the relationship with the investigational product will be assessed to determine the relationship and be judged as, definitively, probably, possibly, unlikely, not related, or not assessable. All SAEs, SARs, and SUSARs will be reported immediately (and certainly no later than 24 h) by the investigator to KCTU. The chief investigator will report relevant SAEs to the ethics committee.

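### Cydar EV is a medical device but harms are categorised under medicines regulations, so a failure during the procedure that injures nobody has no safety outcome or reporting category

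*Protocol article*

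**What the plan says.** All references are to the protocol article.

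- **What the product is.** The abstract and Background {6a} both describe Cydar EV as a CE-marked medical device.
- **Harms, {22}.** "Adverse events will be categorised as per the medicines for human use (Clinical Trials) regulations 2004 and amended regulations 2006". Each adverse event is assessed for its relationship to the product. SAEs, SARs and SUSARs go to KCTU within 24 hours. No other category is on that clock, and none is named for a device malfunction.
- **Outcomes, {12}.** The adverse event outcome is any hospital admission in the year after the repair. No outcome in {7} or {12} counts device failures.
- **Compliance, {11c} and {20c}.** In {11c}: "Reasons for non-compliance could include Cydar EV device failure, Internet failure, surgeon error", followed by further reasons that include failed image upload and a surgeon not trained on Cydar. Section {20c} gives a shorter list that names device failure but not internet or upload failure: "Reasons for non-compliance would include device failure, surgeon error, or failure to communicate correct randomisation allocation to the surgeon". It also says: "Compliance with intervention will be recorded in the source data worksheets and transcribed to the EDC system".
- **DMC, {21a}.** The committee receives recruitment, serious and non-serious adverse events, and a summary of the clinical data to date. Further detail is left to a charter.
- **Safety analysis, {20a}.** Safety outcomes are to be reported as proportions and rates with 95% intervals, exact where suitable.
- **Stated risk, {6a}.** "There are no known additional risks of using Cydar EV in comparison to standard treatment". Then: "Interruption of the Internet connection during the procedure is possible but rare", with a figure of under 0.001% in brackets.

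**The concern.** The failures peculiar to this intervention are loss or misalignment of the overlay, loss of the connection, and images that never reach the system. Such a failure need not injure the patient or lead to an admission, and it may still lengthen the procedure or force the team back to standard imaging. A scheme built on events in patients has no place for it. The protocol does anticipate most of these failures, but only as reasons why the allocated treatment was not delivered.

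At stake is whether the trial will say anything about device reliability as a safety matter. Failures could be collected in full and still be reported only as non-adherence, with no expedited route and no commitment to show them to the one oversight committee that Table 1 lists as unblinded. The article meanwhile offers a very small risk figure for one of these failures, with nothing to support it.

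**Working it through.** **1. Where would a failure without injury be counted?** Take an overlay lost during the procedure, with the operation completed on fluoroscopy and no harm to the patient.

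| Place in the protocol article | Does it capture the event? |
|---|---|
| Adverse event outcome {12} | No. It requires a hospital admission. |
| SAE, SAR, SUSAR {22} | No. No category is named for a malfunction without a patient event. |
| Other outcomes {7}, {12} | Not as a failure. Procedure time may be longer, but the cause is not an outcome. |
| Safety proportions {20a} | Only if the event is defined as a safety outcome, and it is not. |
| Compliance record {11c}, {20c} | Yes, as a reason for non-compliance, held in the EDC. |
| DMC report {21a} | Not named, and not excluded. |

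The event therefore has a place in the data but none in the safety reporting.

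**2. The denominator.** From Sample size {14}: control mean 132.1 min, SD 69.2, ratio of means 1.2, lognormal, 90% power, two-sided 5%.

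- CV = 69.2/132.1 = 0.524; SD on the log scale = √ln(1 + 0.524²) = 0.492.
- n per arm = 2 × [0.492 × (1.960 + 1.282)/ln 1.2]² = 153.3, against 153 stated.
- Inflation: 153/(1 − 0.10) = 170, as stated.

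So between 153 and 170 Cydar-arm procedures can reasonably be assumed.

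**3. What a reported failure proportion would show.** With no failures in n procedures, the exact two-sided 95% upper limit is 1 − 0.025^(1/n).

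- n = 170: 1 − 0.025^(1/170) = 2.1%.
- n = 153: 1 − 0.025^(1/153) = 2.4%.

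The chance of seeing at least one failure in 170 is 1 − (1 − p)^170.

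- True risk 1%: 82%.
- True risk 2%: 97%.

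These risks are illustrative; the article gives no rate for device or upload failure. A common problem would probably show itself, and a rare one would be bounded at about 2%.

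**4. The figure of under 0.001%.** It has no numerator or denominator, so it cannot be reproduced. Assume that it is a risk per procedure, p = 0.00001.

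- Expected interruptions in 170 procedures: 170 × 0.00001 = 0.0017. Chance of at least one: 0.17%.
- Failure-free procedures needed for a one-sided 95% upper bound below 0.001%: ln 0.05/ln(1 − 0.00001) ≈ 299,600.
- For scale, the two studies described in {6a} have 109 + 119 = 228 patients. Even if all were Cydar cases without an interruption (an assumption that favours the figure), the one-sided 95% bound would be 1 − 0.05^(1/228) = 1.3%.

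Neither this trial nor the described studies could confirm the figure.

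**The case against.** The strongest case on the other side is that this is a condensed article. The full protocol (version 1.3), the analysis plan and the DMC charter are not shown, and any of them may deal with device failures. Compliance data reach the EDC, the management group meets at least monthly, and every adverse event is assessed for its relationship to the product, so harm caused by the device is not lost. That much stands, and it rules out several stronger readings that a reader might infer:

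- **That failures will never be estimated or shown to the DMC.** The article is silent on this. A rate can be computed from the EDC, and the clinical summary or charter could include it. What can be said is that failures are not a named outcome or a named DMC item.
- **That the article puts the risk of any device failure below 0.001%.** The figure is attached to internet interruption alone. No rate is given for device failure, upload failure or misalignment.
- **That the two described studies were the source of that figure and fail to support it.** The article does not say where it comes from. The 228-patient bound only shows how large a source would be needed.
- **That the two lists of non-compliance reasons contradict each other on device failures.** Both are worded as examples, and the shorter one excludes nothing. Using the fuller list in both places is tidier, but the difference is not an error.
- **That the per-protocol primary analysis will drop device failures.** It might, but the article does not say which non-compliant cases are excluded.

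The objection does not reach the rule in {22}. That section does not leave the framework to another document; it states one, and the framework stated is for medicines while the product is a device.

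**Conclusion.** The point holds in this form: the harms section applies medicinal-product categories to a medical device, and the failures specific to that device appear only as compliance reasons. As written, a failure during the procedure without patient injury is in no safety outcome and no reporting category, and is not named for the DMC.

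This does not affect the primary comparison, and nothing in the article shows that patients are put at risk. What is lost is modest but useful: a device-failure proportion that could be bounded at about 2.1% with no events in 170 procedures (2.4% in 153). The reading rests on the article's own categories and definitions, and on no fuller device-reporting rule existing in the full protocol.

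The unsupported figure of under 0.001% is a secondary point. The calculation on it assumes a per-procedure risk, and the trial cannot verify it.

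**What to change.** 1. **Section {22}.** Replace the medicinal-product categories with device ones: device-related adverse events, serious or not, and device deficiencies with or without harm. Define deficiency to cover device failure, internet loss, upload failure and overlay misalignment.
2. **Expedited reporting.** Put serious device-related events, and deficiencies that could have led to one, on the existing 24-hour report to KCTU.
3. **Section {21a}.** Name deficiencies as an item in the DMC report.
4. **Section {20a}.** Report the proportion of procedures with a deficiency, among those where Cydar was used or intended (so including control cross-overs to Cydar), with an exact 95% interval, as part of the planned safety analysis.
5. **Section {20c}.** Use the fuller list of reasons from {11c}, so that internet and upload failures are recorded explicitly.
6. **Section {6a}.** Give the source, unit and denominator for the internet-interruption figure, or remove it.

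The cost is protocol wording, one EDC form that re-uses compliance data already recorded, and slight extra reporting work for sites and the trial statistician. Sample size and primary analysis are unchanged.
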